## Abstract

**Background:**

Posttransplant metabolic syndrome (PTMS) is a common contributor to morbidity and mortality among solid organ transplant recipients in the late posttransplant period (≥1 year). Patients diagnosed with PTMS are at a higher risk of cardiovascular disease and frequently experience decreased physical function and health-related quality of life (HRQL). Studies in the early posttransplant period (<1 year) have shown the benefits of facility-based exercise training on physical function and HRQL, but have not evaluated the effects on metabolic risk factors. It remains unclear whether home-based exercise programs are feasible and can be delivered at a sufficient exercise dose to have effects on PTMS. This protocol outlines the methodology of a randomized controlled trial of a partly supervised home-based exercise program in lung transplant (LTx) and orthotopic liver transplant (OLT) recipients.

**Objective:**

This study aims to evaluate the feasibility (ie, recruitment rate, program adherence, attrition, safety, and participant satisfaction) of a 12-week individualized, home-based aerobic and resistance training program in LTx and OLT recipients initiated 12 to 18 months after transplantation, and to assess estimates of intervention efficacy on metabolic risk factors, exercise self-efficacy, and HRQL.

**Methods:**

In total, 20 LTx and 20 OLT recipients with ≥2 cardiometabolic risk factors at 12 to 18 months after transplantation will be randomized to an intervention (home-based exercise training) or control group. The intervention group will receive an individualized exercise prescription comprising aerobic and resistance training, 3 to 5 times a week for 12 weeks. Participants will meet on a weekly basis (via videoconference) with a qualified exercise professional who will supervise exercise progression, provide support, and support exercise self-efficacy. Participants in both study groups will receive a counseling session on healthy eating with a dietitian at the beginning of the intervention. For the primary aim, feasibility will be assessed through recruitment rate, program adherence, satisfaction, attrition, and safety parameters. Secondary outcomes will be measured at baseline and 12 weeks, including assessments of metabolic risk factors (ie, insulin resistance, abdominal obesity, blood pressure, and cholesterol), HRQL, and exercise self-efficacy. Descriptive statistics will be used to summarize program feasibility and effect estimates (means and 95% CIs) for sample size calculations in future trials.

**Results:**

Enrollment started in July 2021. It is estimated that the study period will be 18 months, with data collection to be completed by December 2022.

**Conclusions:**

A partly supervised home-based, individually tailored exercise program that promotes aerobic and resistance training and exercise self-efficacy may be an important intervention for improving the metabolic profile of LTx and OLT recipients with cardiometabolic risk factors. Thus, characterizing the feasibility and effect estimates of home-based exercise constitutes the first step in developing future clinical trials designed to reduce the high morbidity associated with PTMS.

**Trial Registration:**

ClinicalTrials.gov NCT04965142; https://clinicaltrials.gov/ct2/show/NCT04965142

**International Registered Report Identifier (IRRID):**

DERR1-10.2196/35700

## Introduction

### Background

Posttransplant metabolic syndrome (PTMS) is prevalent among solid organ transplant recipients with >25% of lung transplant (LTx) and 50% of orthotopic liver transplant (OLT) recipients developing PTMS within 12-18 months [1,2]. PTMS comprises impaired glucose tolerance, obesity, hypercholesterolemia, and hypertension and has been associated with an increased risk of hospital readmissions and cardiovascular morbidity accompanied by decreased long-term survival [3-5]. LTx and OLT recipients frequently present with risk factors for PTMS, including increased appetite and weight gain along with a reversal of the pretransplant catabolic state, immunosuppression, and physical inactivity [6]. Our research group has shown that in a sample of >2000 OLT recipients in the Toronto Liver Program (1990-2015), 35% had pre-existing, new onset, or transient posttransplant diabetes mellitus, a PTMS risk factor associated with decreased long-term survival [7]. A retrospective evaluation of 227 LTx recipients conducted by our group also demonstrated a significant increase in the prevalence of metabolic risk factors (hypertension, hyperlipidemia, diabetes mellitus, and obesity) by 1 year after transplantation (≥3 factors: 26%) compared with before transplantation (11%) [8].

LTx and OLT recipients have been observed to engage in less physical activity than the general population and report barriers to exercise, including lack of specific exercise guidelines, medication side effects, comorbidities, and inability to access fitness facilities [9,10]. In a cross-sectional survey of 656 solid organ transplant recipients, van Adrichem et al [11] found that only 56% of patients met the physical activity guidelines and engaged in ≥150 minutes per week of moderate aerobic activity after transplantation. A 2019 consensus statement [12] highlighted the importance of strategies to mitigate posttransplant metabolic risk factors with physical training. The recommendation for solid organ transplant recipients is to practice moderate to vigorous intensity physical training (either aerobic or aerobic plus resistance training) 3 to 5 times a week for a minimum of 8 weeks [12].

The posttransplant period offers an opportunity for transplant recipients to derive significant metabolic and functional benefits from exercise, as most of them can train at a greater volume and intensity than in the pretransplant period [13]. In this regard, 24 sessions of 30-minute treadmill exercise sessions were associated with a significant increase in resting energy expenditure in OLT recipients [14]. Moreover, a meta-analysis of 15 randomized controlled trials (RCTs) showed a significant reduction in body fat percentage in OLT recipients (1 trial, 119 patients) who participated in physical exercise training (median −5.40%, 95% CI −8.03% to −2.77%; P<.001) [15]. Most of the exercise programs included in this meta-analysis implemented exercise interventions starting a year after transplantation (program duration between 8 and 24 weeks) and focused on aerobic and strength training.

To date, most exercise interventions in LTx and OLT recipients have been delivered as supervised, facility-based programs within the first 12 months after transplantation [16-19]. However, facility-based programs present challenges for patients [12,20], especially in the late posttransplant period. Given the decreased frequency of clinic visits, relocation requirements, return to work [21], and the interruption of hospital and community-based programs during the COVID-19 pandemic [22], home-based exercise programs can overcome some of these challenges and have been recognized as an important strategy that requires further research [20].

In light of the current challenges to health care delivery because of the COVID-19 pandemic, telerehabilitation and remote exercise interventions are gaining attention as the preferred modalities for promoting physical activity and exercise behaviors among solid organ transplant recipients [23-26]. Only a few studies on home-based exercise programming in the early and late posttransplant periods have been conducted in both LTx [27-29] and OLT [30,31] recipients, and they have suggested benefits to aerobic capacity, quadriceps strength, and health-related quality of life (HRQL). In one of these studies, program adherence in OLT recipients was poor (only 37% of participants completed ≥50% of exercises with bimonthly phone calls) [30], whereas adherence was not assessed in a home-based program with 12 LTx recipients (mean 36 months, SD 33 months after transplantation) [27]. Furthermore, the effects of home-based training on metabolic risks were evaluated in only 1 OLT study, which used a combination of a few personalized sessions and group telehealth classes for exercise and nutritional counseling for a 3-month period and showed a modest improvement in metabolic syndrome and HRQL [32]. However, the optimal structure of counseling, exercise prescription, and effects on metabolic risk factors among solid organ transplant groups remains to be defined [12].

There is limited literature surrounding the experiences of transplant recipients concerning knowledge of, motivation for, and barriers to exercise training, which limits our understanding of the feasibility of real-world implementation. Several strategies to engage participants in exercise interventions and optimize adherence have been explored for chronic diseases [9]. The literature on chronic disease management highlights that adherence can be increased by providing close support by an exercise professional, simplifying the number of exercises, and fostering self-efficacy for exercise [33]. The support and coaching by the exercise professional can be enhanced with the use of telecommunication and the ability of the participants to readily contact the health coach as needed [26,27]. In addition, focusing on four sources of self-efficacy built into an exercise program (mastery, vicarious experiences, verbal feedback, physiological and emotional state) has been shown to significantly improve exercise adherence in patients with cardiometabolic risk factors [34,35] but has not been applied to transplant recipients.

These gaps in knowledge are important to address as optimal effects on PTMS are likely achieved if exercise is performed with sufficient volume (at least moderate intensity, accumulating ≥150 min/week) [36]. However, it remains unclear whether this training dose is optimal or if it can be achieved with a home-based program targeting metabolic risk factors starting at 12-18 months after transplantation, a critical period prognostic of long-term PTMS and cardiovascular morbidity [37]. Before these efficacy questions can be addressed with an appropriately powered RCT, a pilot study evaluating the feasibility of a home-based exercise program is needed.

### Aims

The specific aims of this study are (1) to evaluate the feasibility of a 12-week individualized, home-based aerobic and resistance training program in LTx and OLT recipients at 12-18 months after transplantation and (2) to assess estimates of intervention efficacy on PTMS risk factors, exercise self-efficacy, and HRQL. We hypothesize that we will achieve a recruitment rate of 30% of eligible LTx and OLT recipients, participants in the intervention group will demonstrate an adherence rate of ≥70% to the prescribed exercise dose (including attainment of the prescribed exercise progression over time) and that PTMS risk factors, self-efficacy, and HRQL will be improved in the intervention group compared with the control group.

## Methods

### Design

This paper describes a pilot RCT to assess the feasibility of a phase 3 RCT examining the effects of an individualized, partly supervised, home-based exercise intervention in LTx and OLT recipients. The study is being conducted at the Toronto General Hospital in Toronto, Canada, and ethical approval was obtained from the research ethics board at the University Health Network (study ID: 20-5185). The study was registered at ClinicalTrials.gov NCT04965142. Informed written consent will be obtained from all participants before starting any research activities.

This protocol follows the SPIRIT (Standard Protocol Items: Recommendations for Interventional Trials) guidelines [38], the CONSORT (Consolidated Standards of Reporting Trials) statement [39], and the Consensus on Exercise Reporting Template [40]. Two patient partners are part of the research team, have provided input into the study design, and will contribute support and their lived experience throughout the study. The research team will hold meetings with patient partners every 3 to 6 months to collect feedback on study progress, assess concerns, and work on knowledge translation tools once the study is completed. Modifications to the study protocol will be approved by the research ethics board before implementation, communicated to funding agencies, and outlined in future publications.

### Participants

The study sample will consist of adult LTx and OLT recipients (≥18 years) with at least two or more metabolic risk factors (ie, hypertension, hyperlipidemia, diabetes, and obesity) at 12 to 18 months after transplantation. Exclusion criteria include (1) active cardiovascular disease (eg, recent heart attack, significant coronary artery disease on cardiac catheterization, heart failure, uncontrolled arrhythmias, chest pain, dizziness, or fainting in the last 3 months); (2) neuromuscular disease or orthopedic limitations; and (3) a self-reported active lifestyle (ie, patients achieving ≥150 min/week of moderate-intensity aerobic physical activity).

### Recruitment and Screening

Potential participants will be recruited from posttransplant lung and liver clinics. The study team will identify potential participants at 12 to 18 months after transplantation with ≥2 metabolic risk factors. Participants will be asked by members of their circle of care if they are interested in participating in the study. If agreeable, the research team will contact the prospective participant to confirm eligibility criteria, discuss study participation, and conduct the informed consent process. The study flow of participants is shown in Figure 1.

**Figure 1 figure1:**
[figure not shown]
CONSORT (Consolidated Standards of Reporting Trials) flow diagram.

### Randomization

After the baseline assessment, participants will be randomly allocated using a 1:1 ratio to either the intervention or the control group, stratified by transplant type (ie, liver or lung). The allocation of participants to their groups will be randomized using shuffled, opaque envelopes by a biostatistician with no involvement in data collection in the study. The research team, exercise professionals, and study participants will be aware of the group allocation.

### Study Assessments

#### Overview

Study assessments will be conducted at baseline and 2, 6, and 12 weeks. For a detailed list of assessment procedures by time point, refer to Tables 1 and 2. For participants unable to come on-site, assessments will be performed remotely from participants’ homes, and blood screenings and electrocardiogram assessments will be conducted at local laboratories. During remote assessments, participants will be supervised by the research team using videoconferencing. To ensure the safety and confidentiality of participants undergoing remote assessments, the research team will ascertain the participant’s identity, home address, and phone number. An assessment of the suitability of the participant to perform physical assessments will also be performed before starting any interaction with participants (eg, self-reported breathlessness, dizziness, and chest pain). Participants will be instructed to discontinue exercise testing if they experience any symptoms or feel unwell.

**Table 1 table1:** Assessment of primary study outcomes by time point.

Primary outcomes	Assessment measures	Time point
Recruitment	Consented patients over total of eligible patients approached	During study period
Retention	Measured by attrition throughout the intervention period	During study period
Adherence	Completion of at least 70% of intervention elements	During study period
Satisfaction	Satisfaction survey	Weeks 2, 6, and 12^a^

^a^For usual care, satisfaction will be evaluated at baseline and 12 weeks.

**Table 2 table2:** Assessment of secondary study outcomes by time point.

Secondary outcomes	Assessment measures	Time point
** Metabolic risk factors**		
Glucose tolerance (fasting glucose and HbA1c^a^ test), insulin sensitivity, (fasting insulin and HOMA-IR^b^), cholesterol panel, and C-reactive protein Diabetes, cholesterol, and hypertension medications Abdominal obesity	Blood work and medical charts Blood pressure monitor, charts, and home measurement	Baseline and 12 weeks
Liver fibrosis and steatosis (OLT^c^ patients attending assessments on-site)	Transient elastography (liver stiffness and controlled attenuation parameter for steatosis assessment)	Baseline and 12 weeks
**Clinical parameters**		
Model for end-stage liver disease at transplant Lung allocation score Medication history Electrocardiogram Liver enzymes Hospital admissions Graft function and comorbidities	Medical charts	Baseline and 12 weeks
Physical function	Short performance physical battery	Baseline and 12 weeks
Body composition	Bioelectrical impedance Waist circumference BMI	Baseline and 12 weeks
** Self-reported outcomes**		
Quality of life Barriers to exercise Physical activity behaviors Dietary habits	Short-Form Survey-36 Lifestyle questionnaire Physical Activity Scale for the Elderly Rapid Eating Assessment 3-day nutritional intake	Baseline and 12 weeks
Exercise self-efficacy	Exercise Self-efficacy Scale^d^	Baseline, 2, 6, and 12 weeks^d^

^a^HBA_1c_: hemoglobin A_1c_.

^b^HOMA-IR: homeostatic model assessment for insulin resistance.

^c^OLT: orthotopic liver transplant.

^d^For usual care, exercise self-efficacy will be evaluated at baseline and 12 weeks.

#### Study Arms

Following randomization, all study participants will be provided with a physical activity tracker (Fitbit) and exercise or physical activity logs to monitor exercise adherence and capture lifestyle changes in the intervention group and any contamination in the control group. Given the importance of diet on metabolic risk factors, both study groups will receive a counseling session on healthy eating consistent with the Canadian Food Guide by a registered dietitian, a review of the 3-day food record, and a nutritional handout. Nutritional advice will be tailored to specific metabolic concerns (eg, weight management, diabetes, and hypercholesterolemia). The dietitian will review all participants’ medical histories and pertinent bloodwork as routine care during dietary assessments.

#### Intervention Group

##### Overview

Our exercise program was informed by expert guidelines on exercise prescription in solid organ transplant recipients [12,20,41] and will be delivered by an exercise professional with experience in chronic disease management. Following the baseline assessment and randomization, intervention participants will receive an individualized, home-based exercise program consisting of aerobic and resistance training exercises for 12 weeks. The exercise prescription targets the Canadian Physical Activity guidelines [42], which recommends ≥150 minutes of at least moderate-intensity aerobic training per week and at least two days per week of resistance training for major muscle groups. Daily exercise practice will be unsupervised; however, the exercise professional will provide the exercise prescription during the first training session via videoconference, including the following: an assessment of the participant’s ability to exercise independently in their home environment (eg, review of the participants’ heart rate, blood pressure, and history of any pertinent injuries), demonstration and review of training techniques, and proper use of their Fitbit and exercise equipment.

Participants will also receive a detailed manual describing the importance of exercise and self-management skills for exercise behaviors based on the theory of planned behavior and social cognitive theory adapted from previous studies [43,44]. The manual will highlight the basics of exercise training, the importance of routines, principles related to exercise progression, and photographs with descriptions of the prescribed exercises. After the initial training session, the exercise professional will follow up weekly (via videoconference) with study participants to address potential barriers to exercise, provide motivational support, review symptoms or adverse events during independent training at home, and prescribe training progression. The exercise program will be tailored to the specific and changing needs of the participant, taking into consideration comorbidities, exercise capacity, physical function, and availability of training equipment. Details on exercise prescription for the intervention group are briefly provided and described in Table 3.

**Table 3 table3:** Exercise prescription details for participants in the intervention group.

Modality and frequency	Intensity	Time and volume of exercise	Type of exercise	Progression
Aerobic; 3-5 days/week	Moderate to vigorous (target Borg RPE^a^: 12-14/20) 65% to 85% of age-predicted maximum heart rate	30 minutes Continuous or interval training ≥150 minutes of at least moderate-intensity aerobic training per week	Walking Running Alternating walking and running bouts Biking	Gradual progression of training duration (up to 60 min/session) Increase in walking and running speed or inclination If cycling, increase in revolutions per minute or resistance Increase in prescribed percentage of maximum heart rate
Resistance; 2 days/week	Target Borg RPE: 12-14/20	1-3 sets 6 exercises 10-12 repetitions	Resistance band exercises: Biceps curl Triceps extension Low row Shoulder abduction Body weight exercises: Wall squats Calf raises	Resistance intensity will be increased when 3 sets of 12 repetitions can be completed without difficulty to maintain moderate exertion Increase in resistance band tension Increase in the number of sets, reduction in resting time

^a^RPE: rating of perceived exertion.

##### Aerobic Training

The aerobic exercise prescription comprises three to five 30-minute sessions per week at a moderate intensity of 65% to 85% of the estimated maximal heart rate or 12-14/20 Borg rating of perceived exertion (RPE) scale [45]. The maximum heart rate will be estimated using the formula 207-(0.7×age in years) [46]. Training modalities may include walking outdoors, using a treadmill, cycling with a stationary bicycle, or other modalities available to the participant. The duration of the aerobic training session will be adjusted or divided (eg, 2 sessions of 15 minutes) if the participant has limitations because of comorbidities.

##### Resistance Training

Resistance training will be prescribed for at least two days per week and will focus on general conditioning comprising 6 to 10 exercises targeting the major muscle groups (1-3 sets of 8-12 repetitions). Prescribed resistance training exercises will include a combination of resistance bands with different tension and body-weight exercises. Resistance intensity will be increased when 3 sets of 12 repetitions can be completed without difficulty to maintain moderate exertion despite muscular adaptation (target Borg RPE=12-14/20) [43,44].

##### Safety Precautions for Remote Exercise Training

Participants will be instructed to discontinue exercise training if they experience any symptoms or feel unwell and will be strongly encouraged to immediately contact a member of the research team upon noticing any adverse events. Participants will be advised to reduce the intensity of their training if they reach ≥15 on the Borg RPE scale, if oxygen saturation is less than 85%, or if they experience any symptoms (eg, severe shortness of breath). If participants report chest pain or discomfort (ie, uncomfortable feeling of pressure, pain, squeezing, or heaviness in the chest spreading to the shoulder, arms, neck, and back), they will be instructed to stop and rest and seek emergency assistance if the discomfort persists for 5 minutes.

Participants who communicate medically concerning adverse events (eg, cardiovascular event or disease exacerbation) or contraindications to the exercise program will have their training suspended until clearance is provided by the study physician and the exercise professional. If participants sustain an injury because of participating in the study, the study team will ensure that appropriate medical treatment is received.

Before initiating any interaction with study participants, the study team will perform an objective assessment (ie, by measuring oxygen saturation, blood pressure, and heart rate if participants have a pulse oximeter or a blood pressure monitor at home). A subjective assessment of the study participants (eg, self-reported breathlessness, dizziness, and chest pain) will ascertain their suitability to proceed with testing, training, and progress with the exercise prescription. The study team will discuss with participants aspects of their home environment, availability and suitability of exercise training equipment, home walking space, and any potential safety concerns (eg, footwear, rugs, clutter, and pets). During the internet-based training sessions, participants will be supervised by the study team via a videoconference platform. Participants will be able to book additional sessions with the exercise professional if any concerns or questions arise.

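### The home-training safety rules give two different actions, stop and slow down, for the same trigger, and put severe breathlessness under the milder one

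*Protocol article*

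**What the plan says.** Three consecutive rules in the protocol article, section Safety Precautions for Remote Exercise Training, tell participants what to do during home training.

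- **Stop rule.** "Participants will be instructed to discontinue exercise training if they experience any symptoms or feel unwell". The same sentence urges prompt contact with the research team about adverse events.
- **Reduce-intensity rule.** The next sentence advises lowering intensity on any of three triggers: a Borg rating of 15 or more, a saturation reading under 85%, and a third that it words as "or if they experience any symptoms (eg, severe shortness of breath").
- **Chest-pain rule.** Stop, rest, and seek emergency help if the discomfort lasts 5 minutes.

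The section then suspends training after medically concerning adverse events until clearance is given.

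For remote assessments (Study Assessments, Overview) there is one action only: "Participants will be instructed to discontinue exercise testing if they experience any symptoms or feel unwell".

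On supervision, the Intervention Group overview states: "Daily exercise practice will be unsupervised". The exercise professional holds a first videoconference session and then follows up weekly, among other things to "review symptoms or adverse events during independent training at home".

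**The concern.** A participant who becomes severely breathless during a session has two instructions. One says to end the session. The other names that very symptom and says to ease off, which means continuing to train. The text does not say which applies.

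What is at stake is participant safety. Half of the planned intervention group are lung recipients, for whom severe breathlessness is a plainly relevant symptom. Someone given the second sentence as written could take it as a reason to slow down. The low-saturation trigger may not help everyone: the same section makes the pre-interaction saturation check conditional on the participant having an oximeter at home.

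**Working it through.** There is no stated figure to reproduce. The check compares the rules and then counts how much planned training they govern.

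**1. The rules side by side**

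| Place | Trigger | Action |
|---|---|---|
| Study Assessments, Overview (testing) | any symptoms, or feeling unwell | discontinue |
| Safety Precautions, stop rule (training) | any symptoms, or feeling unwell | discontinue |
| Safety Precautions, reduce-intensity rule (training) | Borg ≥15; saturation <85%; any symptoms, example severe breathlessness | reduce intensity |
| Safety Precautions, chest-pain rule | chest pain or discomfort | stop, rest, emergency help if persistent |

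Of the three sentences that tie an action to any symptoms, two say discontinue and one says reduce intensity.

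**2. Can other text reconcile them?**

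- *A graded scheme (mild: slow down; severe: stop).* None is written, and the only example points the other way.
- *Instructed outranks advised.* The verbs may hint at an order, but none is stated. If the stop rule always prevailed, the symptom clause in the second sentence would never apply.
- *The chest-pain rule.* It has a different trigger.
- *The suspension rule.* It depends on the participant reporting an event, so it does not settle what to do mid-session.

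**3. Planned training under the rule**

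Inputs: 10 participants per arm and organ (Sample Size); 12 weeks; "The aerobic exercise prescription comprises three to five 30-minute sessions per week" (Aerobic Training). Full adherence and retention are assumed.

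- Intervention group: 10 lung + 10 liver = 20; lung share 10/20 = 50%.
- Aerobic sessions per participant: 3 × 12 = 36 to 5 × 12 = 60.
- Group: 20 × 36 = 720 to 20 × 60 = 1,200.
- Lung recipients: 10 × 36 = 360 to 10 × 60 = 600.
- Resistance days per participant: at least 2 × 12 = 24. These may fall on aerobic days, so they are not added to the session count.

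**4. Share without a professional present**

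The number of contacts is an assumption: 12 if the first session counts as week 1, or 13 if 12 weekly follow-ups come after it. As the most favourable case, suppose every contact coincides with an aerobic session.

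- 12 contacts: (36 − 12)/36 = 66.7%; (60 − 12)/60 = 80.0%.
- 13 contacts: (36 − 13)/36 = 63.9%; (60 − 13)/60 = 78.3%.

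The range is 64% to 80%.

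**The case against.** The strongest reply is that an explicit stop rule exists. A participant who stops breaks neither sentence, and a severely breathless person would probably also count as feeling unwell, a trigger that the second sentence does not share. That is true, but it does not help the participant who follows the second sentence and keeps training.

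A second reply is that harm depends on what participants actually receive. There is a detailed manual, a first session with the exercise professional, and standard operating procedures for all protocol elements (Data Management and Quality Assurance). None of these is shown, and they may be clearer. This stands and limits the claim about consequences. It does not remove the conflict, which lies in what the article states and is not a detail left to another document.

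Third, there are more safeguards: symptom checks before study-team interactions, supervised videoconference sessions, bookable extra sessions, weekly symptom review, and daily logs with weekly investigator review (Safety). These are real, but most act before or after an unsupervised session.

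Fourth, the session counts measure training volume, and the ambiguity arises only when symptoms occur. That is correct, and the counts are offered only as exposure to the rule. Fifth, the testing rule governs a supervised activity, so it is weak evidence of what was meant for training. That is also fair; the conflict stands without it.

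**Conclusion.** The concern holds. The safety section assigns the same trigger to stopping and to slowing down in adjacent sentences, illustrates the milder action with a severe symptom, and states no precedence. This should be fixed.

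Confidence in the textual conflict is high. The safety consequence is conditional, because it is unknown whether the manual and procedures repeat the wording, and no number of affected sessions can be given. The exposure figures rest on full adherence and retention; the 64% to 80% share also rests on 12 or 13 professional contacts per participant.

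**What to change.** - Delete the symptom clause, with its breathlessness example, from the reduce-intensity sentence. Add severe shortness of breath expressly to the stop rule. This requires no stopping beyond what the stop rule already demands.
- Keep intensity reduction for a Borg rating of 15 or more.
- Leave the saturation trigger below 85% as written unless the study physician changes it. Whether slowing down is enough at that level is a clinical question for the physician.
- If mild exertional breathlessness at the 12–14 target exertion is meant to lead only to slowing down, name it as the exception to the stop rule.
- Use the same wording in the participant manual, the exercise professional's script and the standard operating procedures.

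The cost is one edited sentence with any named exception, a consistency check of those materials, and research ethics board approval before implementation, which the Design section requires for protocol changes. Design, sample size, visits and analysis are unchanged.
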